#### Qualitative data

Qualitative data will be analyzed with the qualitative content analysis approach [43].

#### Progression criteria

Thresholds for feasibility (recruitment rate, retention rate, and adherence rate) and satisfaction, informing the decision to proceed to an RCT (“Go”) or otherwise to amend the study design [44] were established (see Table 1). Threshold values for recruitment rate [20], retention rate [56, 57], adherence rate [57, 72], and satisfaction [57] were derived from comparable projects addressing the same target population of CGs. Thresholds were set conservatively to account for the anticipated recruitment challenges [9], the duration of the project, and the high probability of change in the informal care arrangement over the course of the study, which would result in participant exclusion.

**Table 1 Tab1:** Progression criteria with benchmarks

Domain	Metric	Go
Recruitment rate	Proportion of eligible CGs consenting to participate	≥ 65%
Retention rate	Proportion of CGs completing the *t*_5_ follow-up data collection	≥ 60%
Adherence rate	Proportion of sessions attended (on-site and digital)	≥ 80%
Satisfaction	Proportion of CGs with a sum score ≥ 23 on the primary outcome measure (ZUF-8), averaged across all data collection time points	≥ 75%

*Note*: *CG* caregiver, *ZUF-8* German version of the Client Satisfaction Questionnaire

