### Statistical analysis

We plan to form two groups of 15 participants each. This compromises between the recommendation for both sample sizes for pilot studies [28] as well as group sizes for group interventions in RCTs [9]. Data will be analyzed within the framework of a mixed-methods approach with a parallel design with the IBM Statistical Package for the Social Sciences (SPSS) software, version 29. Results from the quantitative and qualitative data analyses will be compared accordingly. Quantitative and qualitative findings will be integrated at the interpretation stage.

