## Discussion

With our pAKur project, we are putting into practice the call for interventions and the implementation of research findings on the burden of CGs. We aim to reduce their burden and increase their mental and physical stability. With the knowledge of CGs and experts in the field, we want to develop an outpatient preventive medical service for working CGs and test the CGs’ satisfaction with the service. Additionally, we will determine how to organize the recruitment and the intervention during the pilot, and we will use these organizing principles in the upcoming RCT as well.

Determining the best approach for recruitment will be especially important, as the main issue of the project is expected to be the recruitment of the participants. In general, many CGs do not use support services. CGs are often unaware of their caregiver burden and their own needs or they do not prioritize them [12]. Thus, we expect an initially small number of interested CGs, as they may not recognize their need for a preventive medical service. It is necessary to raise awareness of the impact of caregiver burden on the physical and psychological well-being of CGs, while also providing information about the project in relevant journals, newspapers, and newsletters for CGs [7]. Targeted recruitment of participants through clear project descriptions, as well as the involvement of CGs who support the project or have already participated, may also facilitate recruitment [20].

Due to the short recruitment time, we expect that many CGs will not be able to participate because there is no one to take over for them in providing informal caregiving for their CR or because they lack vacation days [68]. In this case, we plan to postpone one intervention group from April to November to give the CGs more advance notice to help them plan. Additionally, we plan to cooperate with major employers, who can grant special leave for their employed CGs. We have also ensured that the refresher week will take place in 2027 so that CGs can spread the required vacation days over 2 years.

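### The recruitment Go criterion is a consent proportion with no count of caregivers enrolled, so it cannot detect a shortage of interested caregivers

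*Protocol article*

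**What the plan says.** The Statistical analysis section sets the size of the pilot: "We plan to form two groups of 15 participants each", so 30 places.

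The Progression criteria section gives four thresholds in Table 1, with the role of "informing the decision to proceed to an RCT (“Go”) or otherwise to amend the study design". The recruitment row is "Proportion of eligible CGs consenting to participate", with Go at 65% or more. The other rows are the proportion of CGs completing the last follow-up (60%), the proportion of sessions attended (80%) and the proportion of CGs reaching the satisfaction cut-off (75%). The section adds that the thresholds were set conservatively because recruitment is expected to be difficult.

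The Discussion states that "the main issue of the project is expected to be the recruitment of the participants". It names two causes. One is low interest: "Thus, we expect an initially small number of interested CGs, as they may not recognize their need for a preventive medical service". The other is inability to attend: "many CGs will not be able to participate because there is no one to take over for them in providing informal caregiving", or because vacation days are lacking. The responses it lists are operational: outreach, cooperation with employers, and moving one group from April to November.

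Participant characteristics lists the ability to arrange time off and substitute care as an inclusion criterion.

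**The concern.** A progression criterion for recruitment should tell the sponsor whether the later randomized trial can be filled. That depends on how many suitable CGs come forward in a given time and on what share of them agree. Table 1 measures only the second.

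The first expected cause of trouble, few interested CGs, acts on the first component. It lowers the number eligible and the number consenting together and leaves their ratio where it was. The second cause is also hidden if eligibility follows the inclusion criteria literally, because CGs who cannot arrange leave or care are then not eligible and never enter the denominator. What remains visible is refusal by CGs who are already interested and able to come.

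The other three rows do not fill the gap, since each is a proportion among those who enrol. All four rows could therefore read Go in a part-filled pilot. The retention, adherence and satisfaction proportions would then rest on few people, as would the effect-size estimate on the caregiver burden scale that is meant to inform the trial's sample size.

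**Working it through.** **Inputs from the article.** Planned enrolment is 2 × 15 = 30 (Statistical analysis). The recruitment Go is consenting / eligible ≥ 0.65 and the retention Go is ≥ 0.60 (Table 1). The 30 is a pragmatic choice with no power or precision formula behind it, so there is no further figure to reproduce.

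**Input not in the article.** The true consent share *p* among eligible CGs is not given. It is assumed below and varied on both sides of 65%.

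**Step 1: smallest enrolment that reads Go.** For *m* eligible CGs this is *k* = 0.65 × *m*, rounded up.

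| Eligible *m* | Minimum consenting *k* | *k*/*m* | Share of 30 places |
|---|---|---|---|
| 6 | 4 | 66.7% | 13% |
| 12 | 8 | 66.7% | 27% |
| 15 | 10 | 66.7% | 33% |
| 20 | 13 | 65.0% | 43% |
| 30 | 20 | 66.7% | 67% |
| 46 | 30 | 65.2% | 100% |

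The rule has no lower limit on numbers. One third of places filled is only an example.

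**Step 2: the reverse case.** If 47 CGs are eligible and 30 consent, 30/47 = 63.8%. Every place is filled and the row misses Go. Filling all 30 places and also reading Go requires between 30 and 46 eligible CGs.

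**Step 3: how often a small pool reads Go.** With *X* consenting out of *m*, binomial with probability *p*, P(Go) = P(*X* ≥ *k*). With 12 eligible CGs at most 12 of 30 places (40%) can be filled, whatever the consent share. With 38 eligible CGs, 80% consent would give 38 × 0.80 = 30.4, a full pilot.

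| Assumed *p* | *m* = 12, *k* = 8 | *m* = 38, *k* = 25 |
|---|---|---|
| 0.60 | 44% | 29% |
| 0.65 | 58% | 53% |
| 0.75 | 84% | 93% |
| 0.80 | 93% | 99% |

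The result follows *p* far more than it follows the size of the pool. That is proper behaviour for a measure of willingness. It also shows that the row carries almost no information on whether enough CGs were found.

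**Step 4: what a part-filled Go leaves.** With 10 enrolled and retention at its threshold, 10 × 0.60 = 6 CGs complete follow-up across both groups. From 30 enrolled it would be 30 × 0.60 = 18.

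**The case against.** **The thresholds are advisory.** They inform the decision, and the sponsor will know how many places were filled. A reader might infer that four Go readings would launch the trial automatically. The article does not say so. This limits the consequence. It does not remove the point, because criteria are fixed in advance so that the decision does not rest on judgement after the event.

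**The article is condensed.** A recruitment target may stand in the full protocol, and the participant-flow figure is not shown. But Table 1 is presented as the set of criteria and prints both metric and threshold. The point concerns that stated rule.

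**The plan does not predict a third-filled pilot.** This is right. It expects "we expect an initially small number of interested CGs" and plans outreach to raise it. The one-third case illustrates what the rule allows and is not a forecast. The outreach, the employers and the November option do address the shortage, but none is tied to the Go reading.

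**The denominator matters.** If eligible meant meeting only the burden, employment and care-level criteria, CGs unable to arrange leave or care would stay in the denominator and lower the ratio. It would be too strong to say that no definition of eligibility helps. One would help with the second cause. None helps with the first.

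**Consent is itself listed as an inclusion criterion.** A reader might infer that the ratio is 100% by construction. Table 1 plainly treats consent as something an eligible CG may withhold, so that reading is not relied on here.

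**The probabilities rest on an assumption.** This stands. Only at consent above 65% is Go clearly the likelier result in a small pool. With 12 eligible CGs it falls to 44% at 60% consent. The article does not support a claim that the rule nearly always reads Go when recruitment fails.

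**Conclusion.** The point holds in this form. As stated, the recruitment row measures willingness among eligible CGs and is blind to how many were found, which is part of what the plan itself calls its main issue. No other row supplies the missing count.

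The structural conclusion needs no assumption: 10 of 15 passes with a third of places filled, and 30 of 47 fails with all places filled. The probability of a Go in a part-filled pilot does need one. With 12 eligible CGs it runs from 44% to 93% as assumed consent runs from 60% to 80%. The statement about CGs who cannot arrange leave or care rests on reading eligibility by the listed inclusion criteria.

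The conservative setting of the thresholds is no answer, since changing the level of a proportion does not make it respond to numbers. Because the thresholds only inform the decision, this is an improvement that should be made. It is not a flaw that invalidates the pilot.

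**What to change.** Keep the 65% consent proportion. Add a second condition to the recruitment row of Table 1: a prespecified minimum total number enrolled, against the planned 30, within the planned recruitment window. The sponsor should choose the value. A figure such as 20 of 30 is an illustration only. The existing 65% is a consent share taken from a comparable project and gives no basis for a share of places filled.

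Report CGs enrolled per month of recruitment as well, so that the recruitment period of the randomized trial can be derived.

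Two tempting additions are better left out. A minimum per group would treat an uneven preference as recruitment failure, although participants choose their group and that choice is something the pilot studies. The November postponement is a planned contingency, so it should be reported next to the count and should not automatically rule out a Go.

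The cost is one extra condition in the table. Enrolment counts and dates arise from running the study, so no new data, staff or participants are needed. The downside is that a recruitment Go becomes somewhat harder to reach.

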### Participant characteristics

The following inclusion criteria needed to be met by CGs: being able to take part in the intervention by making arrangements for time off (e.g., with their employers) and for caregiving for their CR; being employed or self-employed; being moderately to highly strained by caregiving according to their score on the caregiver scale–short form ([25]; 5–25 points); being of legal age; caring for a CR with care levels 1–4; sufficient knowledge of German to be able to take part in conversations, interviews, and interventions; being able to use our digital services, e.g., by owning a PC, laptop, or smartphone with access to the internet and a webcam and microphone; giving informed consent to take part in the intervention. CGs with acute diseases that need treatment constraining participation will be excluded. For an overview of the participant flow, see Fig. 2.

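### The recruitment-rate Go criterion takes its denominator after leave and substitute care have been required for eligibility, so it cannot register a barrier the plan expects to stop many caregivers

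*Protocol article*

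**What the plan says.** In the section Progression criteria, Table 1 gives the recruitment metric as "Proportion of eligible CGs consenting to participate", with Go at 65% or more. The text there says that the threshold values "were derived from comparable projects addressing the same target population of CGs", and that "Thresholds were set conservatively to account for the anticipated recruitment challenges".

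The section Participant characteristics lists the inclusion criteria. Two of them matter here: "being able to take part in the intervention by making arrangements for time off (e.g., with their employers) and for caregiving for their CR" and "giving informed consent to take part in the intervention". The text gives no separate definition of eligibility for Table 1.

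The Discussion names recruitment as the project's expected main difficulty. It foresees that "many CGs will not be able to participate because there is no one to take over for them in providing informal caregiving", or "because they lack vacation days".

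The section Statistical analysis plans two groups of 15.

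**The concern.** A progression criterion is useful only if the problem it guards against can make it fail. Here the two obstacles named in the Discussion, missing cover and missing leave, are the two that an inclusion criterion requires to be overcome. A caregiver stopped by either one is ineligible, so is not counted as a recruitment failure.

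The definition therefore works against the stated purpose. The thresholds are said to allow for the expected recruitment problems, but this rate does not move with one of the main ones. A Go on recruitment could be recorded while a large share of otherwise suitable caregivers could not attend. That share is what planning of the later RCT needs to know.

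**Working it through.** **Inputs from the article.** Metric: consenting divided by eligible. Threshold: 65%. Planned sample: 2 × 15 = 30. The 65% is a benchmark taken from cited projects, so there is no calculation to reproduce.

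**Assumed inputs.** The documents give neither of these:
- u, the share of otherwise eligible caregivers who cannot arrange leave or cover, taken from 20% to 70%;
- c, the share of those able to attend who consent, taken from 70% to 100%.

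**Three denominators.** Let S be the number of caregivers who meet all criteria other than arrangements and consent. Those able to attend number S(1 − u), and those consenting number S(1 − u)c.

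1. All inclusion criteria applied, consent included: S(1 − u)c / S(1 − u)c = 100%, whatever u and c are.
2. Consent taken out, arrangements kept: S(1 − u)c / S(1 − u) = c. The rate varies with refusal but does not depend on u.
3. Consent and arrangements both taken out: S(1 − u)c / S = c(1 − u).

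**Results for the third denominator, c(1 − u):**

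| | u = 20% | u = 35% | u = 50% | u = 70% |
|---|---|---|---|---|
| c = 100% | 80% | 65% | 50% | 30% |
| c = 90% | 72% | 58.5% | 45% | 27% |
| c = 70% | 56% | 45.5% | 35% | 21% |

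Under the second denominator, each row reads its own c (100%, 90% or 70%) in every column, and so meets 65% throughout. For c = 90% and u = 50% the two rates are 90% and 45%.

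**Where 65% would be missed if it were applied to the third denominator.** This happens when u > 1 − 0.65/c:
- c = 100%: u above 35%;
- c = 90%: u above 27.8%;
- c = 70%: u above 7.1%.

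**In counts.** With 30 consenting, a 65% rule allows at most 46 in the denominator: 30/46 = 65.2% passes and 30/47 = 63.8% does not. Whether the criterion is met can therefore turn on who is counted as eligible.

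**The case against.** A reader might infer from the inclusion list that the criterion is met automatically and that the pilot can learn nothing about recruitment. The documents do not support that. The Table 1 wording makes sense only if eligibility is judged before consent, and listing consent among inclusion criteria is common drafting. The section Study design and setting treats written consent as a step of its own before on-site treatment. On that reading the rate can fall below 65% through refusal, for instance over the costs that the Discussion says caregivers must carry themselves. This part of the objection stands, and the point does not rest on the literal 100%.

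The second objection concerns timing. The criterion speaks of being able to take part, not of arrangements already in place. The Phase 2 section describes people choosing a group after seeing the dates so that they can organise leave and cover. Someone judged eligible early who later fails to arrange these might stay in the denominator as a non-consenter. The participant flow figure, cited directly after the criteria, may settle the order but is not shown. This lowers confidence but does not remove the point: under the criterion as stated, a caregiver without leave or cover does not qualify, and the text has no rule that keeps such a person in the count.

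Third, consent among eligible people is a recognised metric, and the denominator behind the 65% is not visible. That also stands. It would be wrong to set c(1 − u) against 65% and call the result a failed criterion before the benchmark's denominator is known.

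Finally, the plan has measures to ease the barrier: a possible postponement of one group, cooperation with employers, and leave spread over two calendar years. These may reduce u, but they do not make the metric measure it.

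**Conclusion.** The point holds in a limited form. On the article's stated definitions, the recruitment Go criterion can register refusal but not lack of leave or substitute care, which the plan itself expects to keep many caregivers out. The stated purpose of the thresholds and the definition of this one do not agree.

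The gap is a factor of (1 − u), and u is unknown. The figures of 90% against 45% illustrate it under assumed values and are not a forecast. Nor does the wider denominator capture every recruitment risk: caregivers who never come forward are never screened and stay outside either rate.

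This should be fixed, but it does not undermine the study. It concerns one of four criteria that inform the decision to proceed, and it affects no outcome estimate. Confidence is moderate, because the flow figure might define the order of screening.

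**What to change.** For this criterion only:

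- Define the denominator as all screened caregivers who meet the burden, employment, care-level, age, language, digital-access and health criteria, before the arrangement and consent criteria are applied.
- Count inability to arrange time off or cover, and refusal of consent, as not recruited, and tabulate the reasons.
- Confirm which denominator the source of the 65% benchmark used. If it differs, re-set the threshold for the new denominator, or report both rates and state which one carries the Go decision.
- Report the number enrolled against the planned 30.

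The cost is one redefinition in Table 1 and a screening log with reasons. The reported rate will probably look less favourable. The intervention, sample size and measures do not change.

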## Discussion

With our pAKur project, we are putting into practice the call for interventions and the implementation of research findings on the burden of CGs. We aim to reduce their burden and increase their mental and physical stability. With the knowledge of CGs and experts in the field, we want to develop an outpatient preventive medical service for working CGs and test the CGs’ satisfaction with the service. Additionally, we will determine how to organize the recruitment and the intervention during the pilot, and we will use these organizing principles in the upcoming RCT as well.

Determining the best approach for recruitment will be especially important, as the main issue of the project is expected to be the recruitment of the participants. In general, many CGs do not use support services. CGs are often unaware of their caregiver burden and their own needs or they do not prioritize them [12]. Thus, we expect an initially small number of interested CGs, as they may not recognize their need for a preventive medical service. It is necessary to raise awareness of the impact of caregiver burden on the physical and psychological well-being of CGs, while also providing information about the project in relevant journals, newspapers, and newsletters for CGs [7]. Targeted recruitment of participants through clear project descriptions, as well as the involvement of CGs who support the project or have already participated, may also facilitate recruitment [20].

Due to the short recruitment time, we expect that many CGs will not be able to participate because there is no one to take over for them in providing informal caregiving for their CR or because they lack vacation days [68]. In this case, we plan to postpone one intervention group from April to November to give the CGs more advance notice to help them plan. Additionally, we plan to cooperate with major employers, who can grant special leave for their employed CGs. We have also ensured that the refresher week will take place in 2027 so that CGs can spread the required vacation days over 2 years.

In line with outpatient preventive medical service from the statutory health insurance [24], CGs will need to cover some of the costs of the treatment program by themselves, as some costs are not covered (e.g., accommodations, travel fees). This issue might reduce the attractiveness of the program and might also exclude CGs who cannot afford such costs. With the 80€ financial support per night, CGs already need to cover fewer expenses in our treatment program than in the regular outpatient preventive medical service. However, we will raise the daily financial support from 80€ to 100€ per participant. By doing so, we hope to further increase the attractiveness of our treatment program and to enable CGs with different social backgrounds to attend [68].

We expect some dropout due to the length of the intervention (approximately 9 months). The informal caregiving arrangement could change (e.g., if the CR moves into a nursing home or passes away), in which case the CGs will not be allowed to participate, as their data could not be used from that point forward [69]. However, the length of the intervention will allow us to support CGs for a longer period of time as postulated by the literature [31]. As part of the digital support, we can encourage and help implement the changes in behavior into the CGs’ everyday life [8]. We also hope to prevent potential dropout due to motivational issues by providing regular personal contact.

A greater organizational effort is expected regarding the availability, booking, and potential cancellation of hotels in a popular tourist area such as Oberstdorf in Bavaria, Germany. Many preventive treatment programs from the statutory health insurance are embedded in clinics. However, most of these clinics are often fully booked months in advance. By outsourcing the accommodations and some of the activities to facilities in the village, we hope to separate the availability of treatment from the resources in the respective clinic and thus enable more CGs to access preventive treatment programs. Additionally, to support the participants during the booking process, we will provide booking support via our partner from the local tourism board (Tourismus Oberstdorf). Thus, participants will be offered a project-specific landing page where booking is simplified by offering easy access to the cooperating accommodations.

While this pilot has some anticipated difficulties, it also has strengths. First, due to the participatory nature of the development of the outpatient preventive medical service, we can respond specifically to the CGs’ needs. Thus, we can develop a treatment program that is both helpful and realistic. Second, as data will be collected via phone, we expect little missing data. Third, by collecting data over a period of 9 months, we can examine the long-term development of the CGs. Fourth, due to the mixed-methods approach, we expect a comprehensive data collection that allows quantitative results to be explained and expanded by qualitative data. Fifth, with the overall results, we can further adapt the program to the participating CGs’ perspectives and experiences.

The information and knowledge gained from the pilot study, which will focus primarily on feasibility and satisfaction, will be used to plan an RCT that will focus on the sustainable implementation of the developed outpatient preventive medical service.

